## Methods

### Study Design

This is a national, longitudinal, observational study. Potentially eligible patients will be identified using the US Department of Veteran Affairs (VA) Corporate Data Warehouse (CDW) and the COVID-19 Shared Data Resource. A total of 200 patients who have a history of “severe” COVID-19 infection in the previous 3-6 months and at least 1 of the specified comorbidities will be recruited. Severe COVID-19 is defined as requiring hospitalization for acute COVID-19 or its complications. Participants will be required to use the MouthLab device twice daily and to complete monthly surveys administered remotely either by phone or through a web portal. Data will be used to develop a machine learning–based algorithm to detect DEs among patients in the postacute COVID-19 phase.

### Study Setting

The VA is the largest integrated health system in the United States, with over 9 million patients enrolled. VA delivers care to US military veterans across 171 VA Medical Centers and 1113 outpatient care sites across the United States and Puerto Rico, Guam, and other US territories [8]. Nearly 50% of enrolled veterans are aged 65 years or older; 91.1% are male and 8.9% are female; and overall, veterans bear a greater burden of physical and mental health comorbidities than nonveterans [9,10].

### Sample Size

To develop the AIDI algorithm, the study will collect longitudinal parameters that lead up to a DE with the MouthLab device. Because the actual multiparametric changes are unknown and are, in fact, the outcome of the study, the study aims to obtain as much data as possible from those who experience a DE. For this study, we estimate that 100 individual DEs would be sufficient to create a statistical algorithm to predict decompensation. The ultimate goal is to have the algorithm produce no false negatives (ie, if someone is at risk of decompensation while the algorithm says that they are not) and less than 10% false positives (ie, if someone is *not* at risk of decompensation while the algorithm says they are). That is, we do not want to miss any DEs at the cost of having some nonevents classified as being risky.

Al-Aly Z et al [11] observed that the risk and associated burden of pulmonary and extrapulmonary manifestations increase across the disease spectrum of acute COVID-19 infection (from nonhospitalized individuals to hospitalized individuals and then to those admitted to intensive care). The study implemented a comparative approach to examining postacute sequelae in individuals who are hospitalized with COVID-19 versus individuals with seasonal influenza (using a high-dimensional approach and through examination of prespecified outcomes). Results suggested that there is a substantially higher burden of a broad array of postacute sequelae in the individuals who are hospitalized with COVID-19, which provides features that differentiate post–COVID-19 condition (both in the magnitude of risk and the breadth of organ involvement) from postinfluenza viral syndrome [11]. A study by Mainous et al [2] demonstrated a hospitalization rate of 29.8% among survivors of “severe COVID-19.” Given that the AIDI study has defined “decompensation” more broadly than hospitalization alone, we anticipate higher decompensation rates among our study population. Conservatively estimating 1 DE per any participant, with an event rate of 60%, we would need 168 participants to complete the study in order to capture 100 DEs. Since we anticipate up to 15% dropout, we will aim to recruit 200 participants.

### Eligibility Criteria

The inclusion and exclusion criteria are shown in Textbox 1.

Inclusion and exclusion criteria.
**Inclusion criteria**
Aged 18 years and olderWere hospitalized for treatment of acute COVID-19 or its complications in the prior 3-6 monthsAt least one of the following comorbidities:HypertensionAsthmaChronic obstructive pulmonary diseaseHeart failureChronic kidney diseaseDiabetes mellitusEnglish fluencyComfortability with using technologyBasic literacy with electronic platforms
**Exclusion criteria**
Any motor disability that would impede the use of the MouthLab device as required with the left handPregnancyCognitive deficits that would impede the ability to provide informed consentAlzheimer disease or other dementiaPacemakers and implantable cardioverter-defibrillators

### Recruitment

This study will recruit participants from across the country who receive care at the VA. A waiver of the Health Insurance Portability and Accountability Act (HIPAA) and informed consent for screening will be obtained for recruitment. Three modes of recruitment will be used. First, eligible patients will be identified via the CDW and sent letters with information about the study and a number to call if they are interested in learning more. Second, those who have authorized the VA through any partnership programs (eg, COVID-19 research volunteer registry) to receive communication on research opportunities may be contacted for this study. Third, study flyers will be posted at three of the VA’s post–COVID-19 condition clinics. The selection process will include best efforts to ensure equitable inclusion of different races, ethnicities, and age groups among the participants.

### Ethical Considerations

The protocol was approved by the Central Institutional Review Board of the Veterans Healthcare Administration, on December 21, 2022 (1720625-1). Since this is a multisite study, individual institutional review boards at the VA Bedford Healthcare System and the VA Providence Healthcare System also reviewed and approved the study. Informed consent will be obtained from all eligible participants prior to shipping the MouthLab device, administering baseline surveys, and collecting any patient data. Upon obtaining consent, the research team will also obtain HIPAA authorization. No study-related tasks will be performed before obtaining both consent and HIPAA authorization. A member of the research team will send the informed consent form (ICF) to the patient via DocuSign and read through the form with the participants on the WebEx (Cisco) consent call. The person obtaining consent will review the ICF in depth and solicit all questions before the participants sign the ICF via DocuSign. Participants will receive an executed copy via email, and those who prefer to sign a physical copy will be mailed a consent form. This approach will allow participants sufficient time to follow up with questions and discuss before officially signing the consent form. Participants will receive US $85 at the end of months 1-5. At the end of month 6, upon the completion of study tasks (survey and device return), participants will receive US $175. The total potential compensation is US $600, paid by check.

### Study Timeline

The timeline of the study is provided in Table 1.

In addition to MouthLab and survey data (Table 2), data will be collected from the CDW on patient demographics, comorbidities, medications, and potential DEs. The main DEs of interest are any COVID-19–related events that lead to an ED visit, hospitalization, or the need for escalated care (new diagnosis or change in intervention to manage the chronic conditions).

The study will collect information about the index hospitalization, related to COVID-19 either as a primary or secondary diagnosis, from the CDW. This information will include medications (including oxygen therapy), vitals, and the use of mechanical ventilation. Additionally, the index hospitalization will be classified as an intensive care unit–level admission or not.

**Table 1 table1:** Timeline of patient data collection for the Aidar Decompensation Index study.

	Phone screening	Consent	Patient intake form	Training on the MouthLab device	MRC^a^ Dyspnea Scale [12]	Post-COVID-19 Functional Status Scale [13]	VR-12^b^ [14]	User experience survey
First contact and screening	✓							
Consenting and HIPAA^c^ authorization		✓						
Baseline and BP^d^ calibration				✓				
Monthly follow-ups and data collection			✓^e^		✓^f^	✓^f^	✓^e,g^	✓^g^
Termination								

^a^MRC: Medical Research Council.

^b^VR-12: Veterans RAND 12-Item Health Survey.

^c^HIPAA: Health Insurance Portability and Accountability Act.

^d^BP: blood pressure.

^e^First month: patient intake form and first VR-12.

^f^Monthly: MRC Dyspnea Scale and Post COVID-19 Functional Status Scale.

^g^Sixth month: second VR-12 and user experience survey.

**Table 2 table2:** Survey data to be collected for Aidar Decompensation Index study.

Survey data	Instrument or measure	Time points
MRC^a^ Dyspnea Scale (score 1-5)	A 5-point scale that has been used to classify dyspnea, mainly used in grading COPD^b^ progression	Every 4 weeks
Post-COVID-19 Functional Status Scale (0-4 grade scale)	Functional status questionnaire that measures the impact of post–COVID-19 condition on ADL^c^ along with psychological symptoms	Every 4 weeks
VR-12^d^ Quality of Life Assessment	Patient self-report	At the start and end of study
MouthLab Usability Survey	MCQs^e^ to ascertain the information of the physical and usage aspects of the MouthLab device	Study conclusion
User feedback on remote physiological monitoring technology	General perception about remote monitoring technologies (wearable and spot-check)	Study conclusion
Index hospitalization	Collected laboratory data, diagnoses, investigation report, medications, oxygen therapy, clinical notes, and vital signs data	Study conclusion

^a^MRC: Medical Research Council.

^b^COPD: chronic obstructive pulmonary disease.

^c^ADL: activities of daily living.

^d^VR-12: Veterans RAND 12-Item Health Survey.

^e^MCQ: multiple-choice question.

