### Conclusions and Future Work

The findings from this study will result in a predictive algorithm (AIDI) to predict decompensation among high-risk patients who previously had severe COVID-19. In the short term, this could be applied to monitoring such patients during the hospital-to-home transition or for longer periods at home. In the long term, we will adapt and validate the AIDI for monitoring other conditions. Our work will generate insight and guidance for scalable and easy-to-use digital monitoring solutions for remote management of chronic diseases to control disease progression, limiting the impact of comorbidities and, ultimately, improving health outcomes among high-risk populations.

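### The usability survey is scheduled once, at month 6 or study conclusion, so as written it is answered only by participants still in the study then

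*Protocol article*

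**What the plan says.** In the Study Timeline section, the user experience survey has one tick in Table 1. It sits in the monthly follow-up row, and footnote g fixes its timing: "Sixth month: second VR-12 and user experience survey". Table 1 also has a Termination row, which is empty in every column. The instruments repeated at each monthly contact are listed in footnote f: "Monthly: MRC Dyspnea Scale and Post COVID-19 Functional Status Scale". Neither asks about the device.

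Table 2 gives study conclusion as the only time point for the MouthLab Usability Survey and for the feedback on remote monitoring technology. It places the VR-12 at the start and end of the study.

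The Sample Size section states: "Since we anticipate up to 15% dropout, we will aim to recruit 200 participants". Ethical Considerations attaches the last payment to the same point in time: "At the end of month 6, upon the completion of study tasks (survey and device return), participants will receive US $175".

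Usability does not appear among the primary or secondary outcomes in Table 3 (Evaluation of DEs). The stated objective is to develop and validate the AIDI.

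**The concern.** The survey asks about the physical and practical side of a device that participants must use twice a day for six months. Whether someone is still in the study at month 6 may depend in part on how workable they found the device. A survey sent only at that point conditions on a possible consequence of what it is meant to measure. Someone who gave up because the device was awkward has no scheduled opportunity to say so.

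What is at stake is how the usability results can be described. As scheduled, they apply to participants who stayed for six months, and could be mistaken for a result about everyone who enrolled. The primary and secondary outcomes and the prediction model do not depend on this survey.

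**Working it through.** **1. The schedule, side by side.**

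| Place | When the usability survey is given |
|---|---|
| Table 1, monthly follow-up row with footnote g | sixth month |
| Table 1, Termination row | blank |
| Table 1, footnote f (monthly instruments) | not listed |
| Table 2, both device-related surveys | study conclusion |

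The two tables agree on a single late measurement. Neither provides for a survey when a participant leaves early.

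**2. The plan's own numbers.** The Sample Size section says that "with an event rate of 60%, we would need 168 participants to complete the study in order to capture 100 DEs".

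- Completers needed: 100 / 0.60 = 166.7, rounded up to 167, against 168 stated. With 168, the expected number of events is 168 × 0.60 = 100.8.
- Recruitment: 168 / (1 − 0.15) = 197.6, rounded up to 198, against 200 stated.

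Both reproduce to within rounding, so the 15% can be used as the plan's own ceiling for loss before completion.

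**3. How many would have no usability response.** Number missed = N × dropout.

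| Dropout | Missed of 200 | Still in study |
|---|---|---|
| 5% | 10 | 190 |
| 10% | 20 | 180 |
| 15% (planned maximum) | 30 | 170 |

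For the 204 enrolled at submission (Results section), 15% is 204 × 0.15 = 30.6, or about 31.

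**4. What that could do to a usability percentage.** Let c be the favourable share among completers, d the share among early leavers and w the proportion leaving early. The all-enrolled figure is (1 − w)c + wd, so the completer figure differs from it by

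c − [(1 − w)c + wd] = w(c − d).

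The article gives neither c nor d, so the values below are assumptions, with w = 0.15.

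| Assumed c | Gap if d = 0% | d = 25% | d = 50% | d = 75% | d = 100% |
|---|---|---|---|---|---|
| 70% | +10.5 | +6.75 | +3.0 | −0.75 | −4.5 |
| 80% | +12.0 | +8.25 | +4.5 | +0.75 | −3.0 |
| 90% | +13.5 | +9.75 | +6.0 | +2.25 | −1.5 |

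Gaps are in percentage points; a positive value means the completer survey overstates. For example, with c = 80% and d = 25% the all-enrolled figure is 0.85 × 0.80 + 0.15 × 0.25 = 71.75%, a gap of 8.25 points. The sign is positive whenever early leavers rate the device lower than completers. That is the likelier case, but nothing in the article demonstrates it. The gap is proportional to w, so at 5% dropout each entry is one third as large.

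**The case against.** The strongest reply is that this hardly matters. Usability is neither in the objective nor in Table 3, no hypothesis is attached to it, and one closing questionnaire is a common choice for an ancillary measure. That stands as a limit on importance. It does not change what the schedule produces.

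A second reply is that study conclusion in Table 2 could mean the end of each person's own participation, and that withdrawal procedures belong in a full protocol not shown here. The Termination row is empty for every item, so the article may simply not describe termination. This softens the point without removing it: footnote g names the sixth month explicitly, which is a stated rule. If the individual reading was intended, the tables need a line to say so.

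Several stronger readings are tempting and are not supported.

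- *A reader might infer that the survey is biased upward by a known amount.* The direction is plausible, but the range in the working crosses zero and rests wholly on assumed ratings.
- *A reader might infer that the article itself says people stop because the device is hard to handle.* The Limitations section mentions trouble with the device only as a reason why very ill patients may not enrol. No reason for dropout is given anywhere. Some losses in this previously hospitalised population may be through illness or death, and an exit survey would not recover all of those.
- *A reader might infer that the survey is the study's only evidence on usability.* The Strengths section describes a dashboard showing absent data and non-compliance for all participants. That is indirect usage evidence, including on early leavers up to the time they stop. It does not record their opinion or their reason.
- *A reader might infer that the article's ease-of-use statement depends on this survey.* The wording, "scalable and easy-to-use digital monitoring solutions for remote management of chronic diseases", comes from Conclusions and Future Work. It looks forward and is not tied to the survey.
- *A reader might infer that 30 people will certainly be missed.* The 15% is a planning ceiling; the actual number may be lower.

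**Conclusion.** The point holds as a modest one about scheduling and reporting. Tables 1 and 2 place the usability survey only at month 6 or study conclusion, so as written the results describe participants still in the study at that time. At the planned maximum dropout, up to about 30 of 200 would have no usability response. This rests on taking footnote g literally and on no exit procedure being laid down in a fuller document.

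Early leavers may rate the device differently, probably less favourably, but neither the size nor the direction of the resulting bias can be established from the article. The survey timing does not affect AIDI development, the decompensation outcomes or the sample size.

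**What to change.** In Table 1 (footnote g and the Termination row) and Table 2, schedule the usability survey at month 6 or at early termination, whichever comes first. Add a one-line question on the reason for stopping. In the report, show early leavers separately, state how many were not surveyed, and label any result that excludes them as completers only.

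Leave the second VR-12 as a month-6 measure. If a VR-12 is taken at early termination, keep it separate: pooling it with the month-6 values would mix follow-up times and weaken the fixed-interval comparison.

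The cost is a wording change and at most about 30 extra contacts using existing instruments. Some early leavers will not respond. Because 204 participants had been enrolled at submission, those who have already left may be reachable only retrospectively, with the recall problems that brings. The reporting part of the fix does not depend on reaching them.

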### Evaluation of DEs

Data on outcomes (DEs) will be collected at the end of the data collection period via the CDW, records obtained from non-VA hospitalizations and ED visits, and monthly and end-of-study surveys.

A DE is defined as a complication related to organ dysfunction induced by SARS-CoV-19 that establishes the need for a change in treatment or intervention. To identify these events, we will first identify all new diagnoses and treatments, including medications, health care visits, and changes in level of service (eg, outpatient, inpatient, and hospital at home), for each patient during the study period using national CDW data. The data reviewed will be limited to those linked to relevant service types (eg, emergency care, urgent care, primary care, cardiology, and pulmonology). A study staff member will review these outcomes with guidance from the principal investigator or other team member with medical training to establish which are highly likely, somewhat likely, and not likely to be related to COVID-19. The full set of outcomes (Table 3) will be used as one outcome in one approach to the development of the predictive algorithm, and the subsets of highly likely and somewhat likely DEs will be used in a second approach to development.

**Table 3 table3:** Study outcomes.

Outcomes		Instrument or measure
**Primary outcomes**		
	All-cause, higher-level health care use (hospitalization, ED^a^, or urgent care visits within the VA^b^ system)	Participant self-reporting, confirmed through EMRs^c^
	All-cause health care use (within and outside the VA system)	Participant self-reporting, confirmed through record requests and EMRs
	Highly likely COVID-19–related health care use	As evaluated by the PI^d^ and subinvestigators
	Highly likely and somewhat likely COVID-19–related health care use	As evaluated by the PI and subinvestigators

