**Methods:**

Overall, 200 participants will be enrolled. Inclusion criteria are patients in the US Department of Veterans Affairs health care system; “severe” COVID-19 infection during the acute phase, defined as requiring hospitalization, within 3-6 months before enrollment; aged ≥18 years; and having 1 of 6 prespecified chronic conditions. All participants will be instructed to use the MouthLab device to capture daily physiological data and complete monthly symptom surveys. Structured data collection tables will be developed to extract the clinical characteristics of those who experience decompensation events (DEs). The performance of the AIDI will depend on the magnitude of difference in physiological signals between those experiencing DEs and those who do not, as well as the time until a DE (ie, the closer to the event, the easier the prediction). Information about demographics, symptoms (Medical Research Council Dyspnea Scale and Post-COVID-19 Functional Status Scale), comorbidities, and other clinical characteristics will be tagged and added to the biomarker data. The resultant predicted probability of decompensation will be translated into the AIDI, where there will be a linear relationship between the risk score and the AIDI. To improve prediction accuracy, data may be stratified based on biological sex, race, ethnicity, or underlying clinical characteristics into subgroups to determine if there are differences in performance and detection lead times. Using appropriate algorithmic techniques, the study expects the model to have a sensitivity of >80% and a positive predicted value of >70%.

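### Table 3's first primary outcome labels scheduled VA admissions as decompensation, which adds label noise to the all-cause models; the size is unknown and the fix is cheap

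*Protocol article*

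**What the plan says.** Three statements in Methods, Evaluation of DEs, have to be read together.

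- **Outcome.** The first row of Table 3's primary outcomes is "All-cause, higher-level health care use". It covers hospitalizations, emergency department visits and urgent care visits inside the VA. Neither the row nor any other part of the article requires a hospitalization to be unplanned or non-elective.
- **Definition.** "A DE is defined as a complication related to organ dysfunction induced by SARS-CoV-19 that establishes the need for a change in treatment or intervention". The text also treats outcomes and DEs as the same thing: "Data on outcomes (DEs) will be collected at the end of the data collection period".
- **Use.** "The full set of outcomes (Table 3) will be used as one outcome in one approach to the development of the predictive algorithm". The sentence continues that "the subsets of highly likely and somewhat likely DEs will be used in a second approach to development".

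Two features of the section limit the reach of the first row. The records reviewed are confined to service types considered relevant, with emergency, urgent and primary care, cardiology and pulmonology as examples. Each outcome is also graded as highly, somewhat or not likely to be related to COVID-19; the third and fourth primary outcomes rest on that grading.

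**The concern.** The AIDI is meant to recognise short-term physiological change before a DE. Feature Engineering and Selection builds the predictors from recent readings, trends, variability and departure from baseline. Outcome Modeling predicts an event within τ time units of an observation period. The date of a procedure booked weeks ahead is set by a calendar, so the readings before it may be stable. Under the first row of Table 3 the admission is still an event, and through the full set it becomes a positive label.

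Two things are at stake for models built on that label. In training, some stable windows are marked as preceding decompensation, which blurs the contrast the model has to learn. In testing, such events are flagged only as often as any stable window is, so observed sensitivity understates how well the index detects genuine worsening. The label also departs from the article's own definition of a DE.

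**Working it through.** **1. The plan's own figures.** Sample Size assumes one DE per participant and a 60% event rate, and seeks 100 DEs.

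- Completers: 100/0.60 = 166.7, so 167; the plan states 168.
- Expected DEs: 168 × 0.60 = 100.8.
- Recruitment at 15% dropout: 168/(1 − 0.15) = 197.6, so 198; the plan states 200.

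Both figures reproduce within rounding. The sample-size arithmetic is not at fault.

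**2. Ceiling on sensitivity.** Let q be the share of labelled events with no physiological lead-up, and f the false-positive rate, taken as the chance that a stable window is flagged. Suppose the index detects every other event. Then

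maximum sensitivity = (1 − q) × 1 + q × f.

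The documents do not give q, so its range is an assumption. For f, Sample Size sets a goal of fewer than 10% false positives; f = 10% is used as the limit and f = 0 for comparison.

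| q (assumed) | ceiling, f = 0 | ceiling, f = 10% |
|---|---|---|
| 5% | 95% | 95.5% |
| 10% | 90% | 91% |
| 20% | 80% | 82% |
| 25% | 75% | 77.5% |
| 30% | 70% | 73% |

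The ceiling equals 80% at q = 0.20/(1 − f). That is 20% for f = 0, and 0.20/0.90 = 22.2% for f = 10%.

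**3. A detector that is not perfect.** If the index detects 90% of the other events, sensitivity is 0.9(1 − q) + q × f. At f = 10% this gives 82% (q = 10%), 78% (q = 15%) and 74% (q = 20%). The margin above 80% is then used up at a smaller q.

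**4. How many admissions might be planned.** Sample Size cites a hospitalization rate of 29.8%. Applied to 168 completers, 0.298 × 168 = 50.1 hospitalized participants. If 10%, 20% or 30% of these admissions were planned (an assumption), that is 5.0, 10.0 or 15.0. Against 100.8 expected DEs, q is about 5%, 10% or 15%, and the ceilings at f = 10% are 95.5%, 91% and 86.5%. All exceed 80%. This step is only indicative, because it divides first-row admissions by the planned number of DEs, and the two follow different definitions.

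**The case against.** **The plan already has a cause-specific label.** This is largely right. A booked procedure should be graded not likely to be related to COVID-19, which removes it from the third and fourth primary outcomes and from the second development. Pairing a broad label with a graded one is a legitimate choice, because the broad label does not depend on staff judgement. It does not repair the first row or the full-set development. An unplanned condition would keep that advantage, since it needs no attribution to COVID-19.

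**Not every contact is captured.** The service-type restriction may screen out many elective stays under other services. It filters by service and not by planned status, so scheduled cardiology or pulmonology stays remain.

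**The targets are not tied to the first row.** A reader might infer that the plan cannot reach its stated sensitivity: the Abstract says "the study expects the model to have a sensitivity of >80" per cent. The documents do not support that inference. The Abstract names no row of Table 3 for this figure, and Performance Evaluation speaks of detecting COVID-19 DEs and reports sensitivity over a range of cutoffs. Likewise, the goal of no false negatives in Sample Size is worded in terms of people at risk of decompensation, so a stable patient admitted by appointment need not count as a miss.

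**Injury visits.** It is tempting to treat injury-related emergency visits the same way. That goes too far, because some injuries, such as falls, can follow physiological worsening.

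**Level of detail.** Admission-type coding could be left to a fuller document. What the article does state, however, is a DE definition, a primary outcome that departs from it, and the use of that outcome as a label.

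**Conclusion.** The point stands as a defect of definition with a limited consequence. As written, scheduled VA admissions within the relevant service types count as DEs in the first primary outcome and in the full-set development, contrary to the article's definition of a DE. The effect is label noise and a lower attainable sensitivity for the all-cause models at any given false-positive rate. A looser cutoff recovers sensitivity only by adding false alarms.

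The size cannot be derived from the documents. It depends on the assumed q, on f near the 10% goal, and on planned admissions having no lead-up at all; any real precursor would soften the effect. Planned admissions at the shares assumed above would not by themselves bring the ceiling below 80%. This is a cheap improvement to the outcome definition and not evidence that the study will miss its target.

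**What to change.** - In the first row of Table 3, and wherever hospitalization enters the full set (including through the second row, all-cause use inside and outside the VA), count only unplanned admissions by excluding those recorded as elective or scheduled.
- Leave the τ window before an excluded admission unscored, as neither event nor non-event.
- Report the literal all-cause definition as a sensitivity analysis.
- Keep injury visits in the outcome; at most, examine their influence in a sensitivity analysis.

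**Cost.** One extra data filter and a sentence of wording. This assumes that admission type is recorded in the Corporate Data Warehouse; non-VA stays would be classified from the requested records. Labelled events fall by about 5 to 15 hospitalizations if 10–30% are planned, which matters because 100.8 expected DEs leave almost no slack over 100. Events without a lead-up, however, add little to a model of that lead-up.

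**What remains.** The second row, read literally, also admits scheduled outpatient visits. This change does not remove them, so the full set would be cleaner but still broader than the DE definition.
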